### Instruments and outcomes

The primary outcome is the patients’ quality of life as measured by SF-36 [16] and the Minnesota Living with Heart Failure Questionnaire (MLHFQ) [17]. The SF-36 is a generic measure of health impairment, with scores ranging from 0 to 100: zero indicates the worst quality of life and 100 the best. The MLHFQ is specific for chronic heart failure and has 21 questions with scores ranging from 0 to 105: zero indicates best quality of life and 105 the worst. Quality of life is assessed at baseline and at 7, 13 and 19 months by the patients, or their main caregiver, within 7 days of their appointment with their GP. A score of < 24 on the MLHFQ signifies a good quality of life, a score between 24 and 45 signifies a moderate quality of life, and a score > 45 signifies a poor quality of life [18]. We will assess these cut-off scores to interpret results in clinical terms. We were unable to find published cut-off information for the SF-36 health scores.

The secondary outcomes are: all-cause and heart-failure-associated mortality; all-cause and heart-failure-associated hospitalization, number of days in hospital; the cumulative number of all cause death or HF hospitalizations and the cumulative number of days of hospitalisation; adherence with therapy; evolution of NYHA heart failure stage; evolution of treatment; and changes in weight and body mass index (BMI) at 19 months. We will assess guideline adherence of treatment at baseline and during the follow-up period. Patient adherence with therapy will be assessed by the patients themselves with a self-administrated questionnaire (validated in French) at baseline and at the end of follow-up period [19].

Should the planned follow-up appointment be missed, the reason is identified and categorised as follows: lost-to-follow-up; death; unable to attend for another reason. Hospitalisations and mortality will be recorded by GPs at each planned visiting case report form.

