### GP recruitment and patient enrolment

GPs are eligible to participate in the trial if they provide in their practice standard care as opposed to exclusively providing alternative medicine such as acupuncture or homeopathy. Participating GPs must sign an informed consent form and agree to implement the study protocol. Potentially eligible GPs are identified via the Regional Primary Care Physician Association with an address database.

In both groups, GPs identify eligible CHF patients and ask them to participate. The GPs recruit the first eligible patients to participate in the clinical trial until they have included at least five patients. The inclusion period lasts one year. The GPs in the two groups receive the same compensation for their participation. The GP shares an information sheet and a consent form with the patients. During the inclusion visit, the GP explains the aim of the clinical trial, i.e. understand and improve treatment of patients with heart failure, without describing the objectives. Patients willing to participate sign the consent form at home within seven days of the visit and send it to the data management centre with the first two quality of life questionnaires.

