#### Statistical analysis

The statistician will be blinded with regard to treatment allocation. The responses to the questionnaire will be entered into a customised Access database (Microsoft, Redmond, Wash, US). Analyses will be made using Stata, version 13 (StataCorp, College Station, Tex, US). If necessary, an adjustment to accommodate differences between the baseline characteristics of the groups will be made. Continuous data will be presented as mean ± standard deviation (SD). The comparisons between study groups will be analysed using Chi-square or Fisher's exact test for categorical variables, and Student's or Mann–Whitney tests for quantitative variables, with normality verified by the Shapiro-Wilk test and homoscedasticity by the Fisher-Snedecor test. The correlation between SF-36 and MLHFQ will be assessed using Pearson’s correlation coefficient. Hierarchical linear regression models with random-effects levels for practice, individuals within practices and repeated measurements per individual (slope and intercept) will be used to estimate the effects of the intervention on SF-36 and MLHFQ scores for the post-baseline time points. These models will include an interaction factor between both the randomisation group and the particular time point, and will be adjusted for baseline SF-36 scores, age, gender, diagnosis, smoking history, treatment and socioeconomic status. Intra-class correlation coefficients will be presented by group. The secondary analyses will compare deaths (overall and due to heart failure) using Kaplan-Meier estimation and the Cox proportional-hazards regression model, hospitalisations (overall and due to heart failure), NYHA stage, treatment, adherence, weight and obesity between the groups with longitudinal random-effects models described previously. Estimation methods developed by Verbeke and Molenberghs will be used to account for missing data (GPs and patients) [25].

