For instance, one study on 240 patients with a mean age of 70 years and a majority of NYHA stage III (96.4%) reported baseline SF-36 mean scores of 45.1 in the intervention group and 46.8 in the control group [14]. The baseline MLHFQ mean scores were 42.5 and 42.6, respectively. In another study on 200 patients with a mean age of 63.5 years and a majority of patients with NYHA stage II-III (94%; 6% had stage IV), the baseline MLHFQ mean scores were 64.3 and 62.4 in the intervention and control groups, respectively [10]. In a study comparing home and hospital follow-up in 280 patients with a mean age of 71 years and slightly fewer patients with NYHA stage II-III (85%; 15% had stage IV), the baseline MLHFQ scores were 48.8 and 46.0, respectively [11]. In three other studies with 89%, 50% and 80% patients with NYHA stage III or IV, the mean MLHFQ scores were 49.3, 51.8, and 44.7, respectively [12,13,23]. Our patients will probably be older, with a better quality of life than the patients in all these studies because they are recruited in a primary care setting with NYHA stage I, II or III.

To our knowledge only one other cluster-randomised trial that measured the impact of a patient education programme by GPs has been published [23]. A total of 283 patients (mean = 76.3 years) were included: stage I – 1.8%; stage II – 7%; stage III – 38.9%; and stage IV – 50.5%. The mean MLHFQ score was 49.1 and 49.9 in the intervention and control groups, respectively.

The frequency of the visits in the ETIC trial, every 3 months, was similar to the standard of care; 87% of patients with heart failure meet their GP at least four times a year [38]. However, the educational aspects of the visits can be difficult for some of the GPs in the intervention group.

This study has limitations. The GP randomisation was done before the patient inclusions. The patients in the two groups might be different because the training received by the GPs in the intervention group may make them feel more competent and therefore, more inclined to include more severely ill patients. To avoid this bias, we could recruit randomised GPs after they had included their patients, using the ‘Zelen’ method [39]. Unfortunately, this has not been possible because the inclusion period lasts one year and the follow-up 19 months; regarding heart failure patient life expectancy, it would not be relevant [5].

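### The model for the MLHFQ, one of two primary scores, adjusts for baseline SF-36 but not for baseline MLHFQ

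*Protocol article*

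**What the plan says.** Under Instruments and outcomes, the protocol article names SF-36 and MLHFQ together as the primary outcome. The schedule there is: "Quality of life is assessed at baseline and at 7, 13 and 19 months by the patients". Under GP recruitment and patient enrolment, patients sign the consent form and "send it to the data management centre with the first two quality of life questionnaires". Baseline MLHFQ is therefore available.

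Under Statistical analysis, hierarchical linear models with random effects for practice and patient are used to "estimate the effects of the intervention on SF-36 and MLHFQ scores for the post-baseline time points". The next sentence covers all of these models and says that they "will be adjusted for baseline SF-36 scores, age, gender, diagnosis, smoking history, treatment and socioeconomic status". No other baseline quality-of-life score is listed.

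The same section has one general provision: "If necessary, an adjustment to accommodate differences between the baseline characteristics of the groups will be made". The Discussion repeats the idea of adjusting for differences between the groups, again without naming variables. As a limitation it also states: "The GP randomisation was done before the patient inclusions". It accepts that trained GPs may include sicker patients.

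**The concern.** A single covariate list serves two outcomes, and its only baseline quality-of-life term belongs to one of them. The repeated-measures structure does not fill the gap. The outcome vector starts after baseline, so the random intercept and slope are estimated without the baseline MLHFQ value.

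A score's own baseline is usually the strongest single predictor of its later values. In an individually randomised trial with concealed allocation, leaving it out would mainly waste precision. Here there is also a route to bias. Intervention GPs learn the inclusion criteria at the same workshop that trains them in patient education, so they recruit knowing their arm. If they enrol sicker patients, as the Discussion allows, baseline MLHFQ will be higher (worse) in the intervention arm and a real benefit could be masked. NYHA stage is not named in the list, and the term diagnosis is not defined. The variable best suited to the acknowledged problem is therefore absent from the model of the disease-specific score.

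**Working it through.** **Wording check.** The outcomes of the models are post-baseline SF-36 and post-baseline MLHFQ. Their covariates are baseline SF-36 plus six other named factors. Baseline MLHFQ appears on neither side.

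**The plan's own figure.** The article asks for 200 patients per group (40 practices of 5). A 12-point difference at effect size 0.6 implies an SD of 12/0.6 = 20. With 90% power and 5% two-sided error this needs 59 per arm.

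- Design effect 1 + (5 − 1) × ICC, for ICC 0.10 to 0.20: 1.4 to 1.8, giving 83 to 107 per arm.
- Dividing by 0.8 for 20% dropout: 104 to 134.
- Dividing by 0.8 × 0.8 = 0.64, for dropout of both GPs and patients: 130 to 168.

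These inputs do not reproduce 200; the stated number is larger than they require. Power at effect size 0.6 is 0.994 to 0.999 with 200 per arm. It is 0.967 to 0.988 with 128 per arm (32 practices of 4). None of this takes credit for baseline adjustment. The concern does not depend on this figure, but it shows how much precision is spare.

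**Assumptions for the size of the effect.** The documents give no correlations. SF-36 and MLHFQ run in opposite directions, so absolute values are used:

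- *a*, baseline MLHFQ with follow-up MLHFQ: 0.5 to 0.7
- *s*, baseline SF-36 with follow-up MLHFQ: 0.3 to 0.5
- *c*, baseline SF-36 with baseline MLHFQ: 0.5 to 0.7

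Clustering, repeated visits and the other covariates are ignored. The SDs at baseline and follow-up are taken as similar.

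**Precision.**

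- Replacing SF-36 by the score's own baseline multiplies residual variance by (1 − a²)/(1 − s²). At a = 0.6, s = 0.4 this is 0.64/0.84 = 0.762, a 24% reduction. 1/0.762 = 1.31, so it is worth about 31% more patients. The range is 0.56 (a = 0.7, s = 0.3) to 1.00 (a = s = 0.5).
- Adding the own baseline to SF-36 uses R² = (a² + s² − 2asc)/(1 − c²). At 0.6, 0.4, 0.6 this is (0.36 + 0.16 − 0.288)/0.64 = 0.3625. The ratio is 0.6375/0.84 = 0.759. Over the whole grid it is 0.48 to 0.94.

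**Bias.** Each point of baseline MLHFQ imbalance not explained by baseline SF-36 carries b = (a − sc)/(1 − c²) points into the treatment effect.

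| a | s | c | b | Bias from a 5-point unshared imbalance |
|---|---|---|---|---|
| 0.5 | 0.4 | 0.6 | 0.26/0.64 = 0.41 | 2.0 |
| 0.6 | 0.4 | 0.6 | 0.36/0.64 = 0.56 | 2.8 |
| 0.7 | 0.4 | 0.6 | 0.46/0.64 = 0.72 | 3.6 |
| 0.5 | 0.5 | 0.7 | 0.15/0.51 = 0.29 | 1.5 (lowest) |
| 0.7 | 0.3 | 0.7 | 0.49/0.51 = 0.96 | 4.8 (highest) |

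With c fixed at 0.6 and s varied over 0.3 to 0.5, b runs from 0.31 to 0.81. The 5-point imbalance is illustrative.

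**If both scores shift together.** Suppose sicker recruitment moves both baselines by the same number of SDs, with a = 0.6, s = 0.4, c = 0.6. SF-36 then accounts for 0.6 of the MLHFQ shift and 0.4 remains. A 5-point MLHFQ imbalance leaves 5 × 0.4 × 0.5625 = 1.1 points.

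**The case against.** Four points can fairly be made against the concern.

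1. **The general adjustment clause could bring baseline MLHFQ in.** It could, but it applies only if judged necessary after the groups have been compared, and it names no variable. It does not prespecify the covariate, and it leaves the model of a primary score open to a data-dependent choice.
2. **The sentence may be shorthand or a slip for the baseline of the score analysed.** This is a journal article, and a separate analysis plan may say it correctly. That is quite possible, but nothing in the article supports the reading. The list is explicit, so this is a stated choice and not a detail left out in condensing.
3. **Precision is not under threat at the plan's own inputs.** This stands. Power is well above 90%, and the assumed correlations include a case with no precision loss. Joint adjustment for several SF-36 domains might also explain more than a single correlation suggests.
4. **SF-36 is a partial proxy, and own-baseline adjustment only partly repairs selective recruitment.** This stands too. General severity would probably move both questionnaires, and the residual bias would then be small. But the article itself describes one instrument as generic and the other as disease-specific, and plans to assess how far they correlate. How good the proxy is remains unknown.

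These points lower the urgency. They do not make the list right for MLHFQ.

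**Conclusion.** The concern holds. As written, one of the two primary scores is modelled without its own baseline, although that baseline is collected. Under the assumed correlations, replacing SF-36 with the own baseline reduces residual variance by 0% to 44% (24% at central values). Adding it to SF-36 reduces residual variance by 6% to 52%. Without it, an unshared 5-point imbalance leaves about 1.5 to 4.8 points of bias against the 12-point target, and about 1.1 points in the shared-shift example. Whether such imbalance exists cannot be known from the document. The model is not invalid in itself, and spare power covers the precision loss. The case for correcting it rests on recruitment after randomisation, which makes baseline imbalance a risk that the article itself acknowledges.

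**What to change.** Replace the baseline term in the covariate sentence with wording such as: each model is adjusted for the baseline value of the score being analysed, that is, baseline MLHFQ for MLHFQ and the baseline of the same domain for each SF-36 domain. Keep the other listed covariates. State whether baseline SF-36 also stays in the MLHFQ model; at central values it hardly matters (variance ratio 0.759 with it, 0.762 without). Baseline MLHFQ should not depend on the conditional adjustment clause.

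The cost is one sentence in the analysis section, and in the analysis plan if it carries the same list. No new data are needed and the sample size is unchanged. The change should be made and dated before the statistician is unblinded.

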**Methods:**

A randomised, cluster controlled trial, stratified over 4 areas of the Auvergne region in France comparing intervention and control groups. The inclusion criteria are: patients older than 50 years with New York Heart Association (NYHA) stage I, II, or III heart failure, with reduced ejection fraction or with preserved ejection fraction. Heart failure should be confirmed by the patient’s cardiologist according to the European Society of Cardiology guidelines criteria. The exclusion criteria include: severe cognitive disorders, living in an institution, participating in another clinical trial, having NYHA stage IV heart failure, or a lack of French language skills. The complex intervention consists of training at the GP practice with an interactive 2-day workshop to provide a patient’s education programme. GPs are trained to perform case management, lifestyle counselling and motivational interviewing, to educate patients on the main topics including clinical alarm signs, physical activity, diet and cardiovascular risk factors. The patients’ education sessions are scheduled at 1, 4, 7, 10, 13 and 19 months following the start of the trial. The primary outcome to be assessed is the impact on the quality of life as determined using two questionnaires: the Minnesota Living with Heart Failure Questionnaire and SF-36. To detect a difference in the mean quality of life at 19 months, we anticipate studying a minimum of 400 patients from 80 GPs.

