## Methods

### Study design and randomisation

The global study design is presented in Figure 1. ETIC is a cluster-randomised, controlled clinical trial with general practices as the unit of randomisation (Figure 2). The randomisation list was drawn up with the software Stata, version 10 (StataCorp, College Station, Texas, US) by the biostatistician before the start of the trial. A cluster design was chosen for pragmatic reasons and to avoid contamination bias. All GPs who volunteered were randomised and the patients did not know to which group their GP had been assigned. GPs that were located within the same practice represented a cluster and such GPs were placed in the same group to avoid cross-contamination. The trial is being carried out across the Auvergne in France, with stratification according to the 4 departments (administrative areas) in this region.

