### Statistical considerations

#### Sample size calculation and power analysis

The sample size required must accommodate the need to detect a difference between the intervention and control groups in the mean quality of life (sample size estimated for each domain of SF-36 and for the MLHFQ score) of 12 points with 90% power and 5% two-sided type 1 error taking into account clustering by practice (intra-cluster correlation considered to be between 0.10 and 0.20) [22], and an estimated 20% dropout rate for GPs and patients. As there is negligible information in the literature regarding SF-36 and MLHFQ assessment in intervention studies, a difference of 12 points was chosen using Brotons’ work [23] and the recommendations of Cohen [24] regarding variability of the quality of life indicators [16]. Estimation of the effect size (ES) can be achieved by a literature search, expert knowledge or using pilot studies. It is also possible to explore several scenarios using conventional effect sizes: small (ES = 0.2), medium (ES = 0.5) and high (ES = 0.8). Variability in the quality of life indicators is fixed for MLHFQ and SF-36 and corresponds to an effect size of ≥ 0.6 [17,24]. With these simulations, it is estimated that 40 general practices recruiting five patients each are required per group, therefore 200 patients per group. Overall, 400 patients from 80 GPs will be recruited.

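### The quality-of-life models omit department, the stratification factor, so any between-department variance makes intervals too wide and tests conservative

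*Protocol article*

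**What the plan says.** The Protocol article describes a "cluster-randomised, controlled clinical trial with general practices as the unit of randomisation" (Study design and randomisation), carried out "with stratification according to the 4 departments (administrative areas) in this region". The abstract says the same: "stratified over 4 areas of the Auvergne region in France comparing intervention and control groups".

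The Statistical analysis section then fixes the model for SF-36 and MLHFQ scores. The random part has "random-effects levels for practice, individuals within practices and repeated measurements per individual (slope and intercept". The fixed part has a group-by-time interaction, and the models "will be adjusted for baseline SF-36 scores, age, gender, diagnosis, smoking history, treatment and socioeconomic status". Department is in neither part and appears nowhere else in the analysis text. Hospitalisations, NYHA stage, treatment, adherence, weight and obesity are to be compared with the random-effects models already described, so on a plain reading they carry the same omission.

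One sentence allows further adjustment: "If necessary, an adjustment to accommodate differences between the baseline characteristics of the groups will be made". It does not name department.

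**The concern.** Stratifying by department takes between-department variation out of the true sampling variance of the comparison between arms, because each department contributes practices to both. A model without department does not know this. It counts department differences as ordinary variation between practices and reports a standard error larger than the one the design delivers.

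The consequences are confidence intervals wider than they should be, a true type I error below the nominal 5%, and some loss of power. Interval width matters here because the Discussion says that interpretation will look at the size of the effect and its clinical relevance, not only at significance.

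The conditional adjustment clause does not help. It is triggered by differences seen between the groups at baseline, and a factor balanced by design would not normally trigger it.

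**Working it through.** **Inputs from the article (Sample size calculation and power analysis).** The target is a difference "of 12 points with 90% power and 5% two-sided type 1 error taking into account clustering by practice", with "intra-cluster correlation considered to be between 0.10 and 0.20". The effect size is at least 0.6, with 40 practices of 5 patients per group and 20% dropout of GPs and patients.

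**Assumptions.** The share *s* of between-practice variance due to department is not given, so 0%, 10%, 25% and 50% are shown. Departments are taken as equal in size, with equal allocation to the arms within each.

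**The plan's own figure.** The unclustered size is 2 × (1.960 + 1.282)² / 0.6² = 58.4, so 59 per group. The design effect 1 + (5 − 1) × ICC is 1.4 to 1.8, giving 83 to 107. Dividing by 0.8 gives 104 to 134, and dividing by 0.8 × 0.8 gives 130 to 168. The stated 200 per group exceeds all of these. That mismatch is a separate matter, and the point here does not depend on it. It does explain why power is ample at 0.6, and it shows that the calculation credits no gain from stratification.

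**Standard error without covariates.** With total variance 1 and *m* patients per practice, a practice mean has variance ICC + (1 − ICC)/*m*. Under stratification the part that drives the treatment contrast is ICC(1 − *s*) + (1 − ICC)/*m*. The inflation from omitting department is the square root of the first over the second. With *m* = 5 × 0.8 = 4:

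| Share *s* | ICC 0.10 | ICC 0.20 |
|---|---|---|
| 0% | √(0.325/0.325) = 1.000 | √(0.40/0.40) = 1.000 |
| 10% | √(0.325/0.315) = 1.016 | √(0.40/0.38) = 1.026 |
| 25% | √(0.325/0.300) = 1.041 | √(0.40/0.35) = 1.069 |
| 50% | √(0.325/0.275) = 1.087 | √(0.40/0.30) = 1.155 |

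Simulation with 80 practices at ICC 0.20 (4,000 trials per setting) gave 1.027, 1.071 and 1.160 for the last three rows. The small excess is a degrees-of-freedom effect. For the last row, (0.30 + 0.10 × 80/78)/0.30 = 1.342, whose square root is 1.158. The ranges are therefore about 0%, 2-3%, 4-7% and 9-16%.

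**Type I error.** Practice means were simulated at the full planned size (40 practices of 5 per arm, 20,000 trials per setting):

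| Share | Without department, ICC 0.10 / 0.20 | With department, ICC 0.10 / 0.20 |
|---|---|---|
| 0% | 0.051 / 0.050 | 0.051 / 0.050 |
| 10% | 0.046 / 0.043 | 0.050 / 0.048 |
| 25% | 0.039 / 0.034 | 0.048 / 0.051 |
| 50% | 0.030 / 0.020 | 0.049 / 0.049 |

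**Power at the planned effect size of 0.6.** At 40 × 5 per arm, power is at least 0.993 with or without department. After 20% loss of both practices and patients (32 × 4 per arm), it is 0.963 to 0.991 without department and 0.963 to 0.995 with it. The largest gain is 0.979 to 0.990, at ICC 0.20 and a 50% share.

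**Power at a smaller effect.** At 0.45, an assumption and not the plan's figure, the gain at 32 × 4 runs from 0 to about 7 points. The largest is 0.831 to 0.898, again at ICC 0.20 and a 50% share.

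**Allowing for baseline score.** As an illustration, suppose department and practice effects persist from baseline to follow-up, the within-practice correlation between the two is 0.6, ICC is 0.20 and *m* = 4. Adjusting with slope 0.6 leaves practice variance 0.4² × 0.20 = 0.032 and patient-level variance 0.80 × (1 − 0.36)/4 = 0.128, in total 0.160. For shares of 10%, 25% and 50% the inflation is √(0.160/0.1568) = 1.010, √(0.160/0.152) = 1.026 and √(0.160/0.144) = 1.054. That is between a third and two-fifths of the unadjusted inflation.

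**The case against.** The best defence is that the error is in the safe direction and may be small. The estimate is unbiased and type I error is not inflated. Nothing in the article suggests that departments of one region account for a quarter or a half of the variation between practices, and at a share of zero the omission costs nothing. The planned adjustment for baseline score would probably absorb much of any stable difference. All of this stands, and it limits the weight of the point.

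A second defence is that such detail belongs in a statistical analysis plan that is not shown. This does not stand for the quality-of-life models. The article is not silent on adjustment: it names seven covariates, down to smoking history and socioeconomic status, without the factor used in the randomisation. The Discussion's remark on multivariate adjustment also concerns differences between the groups.

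Three stronger readings are tempting but not supported:

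- A reader might infer that the stratification is thrown away. The balance it gives between arms is kept whatever the model; only the matching precision in the standard error is lost.
- A reader might infer that the trial loses material power. At the planned effect size it does not.
- A reader might extend the criticism to the Cox model for deaths. The article gives that model no covariate list, so its adjustment is simply not described, and a condensed article may leave that to the full plan.

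**Conclusion.** The point holds as an inconsistency between design and analysis, of minor to moderate weight. The omission itself is plain in the text. Its consequence is certain in direction (standard error too large, intervals too wide, test somewhat conservative) but uncertain in size.

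The figures of 2-3%, 4-7% and 9-16% rest on assumed department shares of 10%, 25% and 50%, equal departments, 4 evaluable patients per practice and no covariate adjustment. They are better read as upper values for each share, since baseline adjustment is planned. The power gain at an effect size of 0.6 is about 1 point or less. The case for change is therefore correct intervals and p-values, with some added precision if the true effect is smaller than planned. The required sample size does not change.

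**What to change.** Add department as a fixed effect with four levels to the hierarchical models for SF-36 and MLHFQ, and to the secondary random-effects models that refer back to them. State this before allocation is unblinded, as a fixed part of the model and not under the conditional adjustment clause.

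The cost is 3 degrees of freedom among about 80 practices. Department is already known for every practice because the randomisation used it, so no new data are needed.

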## Discussion

ETIC is one of the few trials that involving only GPs [27]. Although multidisciplinary patient education programmes are probably more effective [28], the current healthcare organisation in France makes large-scale implementation of this type of intervention difficult, if not impossible. The idea behind ETIC is to evaluate a complex intervention including GP’s 2-day workshop and patient’s education programme in primary care in the current context of healthcare organisation in France to implement education into daily routine.

In Europe, most of the published trials regarding patient education programmes involve hospitalised or younger patients with a profile which is different from patients seen in primary care [29]. In a meta-analysis of randomised controlled trials involving patients with heart failure [30], the mean age of the patients was 61.4 years. In a recent Italian epidemiological study of primary care of patients with chronic heart failure, the mean age was 78.5 years [31]; our study population will probably have a comparable age.

In the ETIC trial, two different quality of life questionnaires are being used, one generic, the SF-36, and the other specific for chronic heart failure, the MLHFQ. The SF-36 questionnaire was chosen because the French version has been validated and it evaluates both physical and mental aspects of the quality of life, taking into consideration cultural differences [16,32]. The MLHFQ questionnaire was chosen because it is specific for patients with CHF, it is also validated in French and it accommodates psychometric properties [33]. In addition, it is recommended for initial use in clinical research [34], has been validated in primary care and is simple and fast to use [17].

The intervention in ETIC is novel because it is standardised with the topics generally used (clinical alarm signs, physical activity, diet and cardiovascular risk factors) [35], but it also involves a holistic approach, centred on the patients’ needs and feelings and taking into consideration their comorbidities and the representations of their disease [36]. The first and subsequent patient education sessions are based on, respectively, educational diagnosis and changes in habits, desires and worries about discussing specific topics, such as smoking habits [21,37].

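### Kaplan-Meier is named for heart-failure death, where 1-KM slightly overstates the absolute risk; secondarily, the Cox clause for deaths names no practice term

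*Protocol article*

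**What the plan says.** The Instruments and outcomes section lists "all-cause and heart-failure-associated mortality" among the secondary outcomes. Statistical analysis assigns the method for both: the trial will "compare deaths (overall and due to heart failure) using Kaplan-Meier estimation and the Cox proportional-hazards regression model". No competing-risk estimator is named.

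On clustering, Study design and randomisation describes a "cluster-randomised, controlled clinical trial with general practices as the unit of randomisation". The sample size section allows for clustering and states that "40 general practices recruiting five patients each are required per group, therefore 200 patients per group". In Statistical analysis, the linear models for SF-36 and MLHFQ have a random effect for practice. The same sentence that deals with deaths then lists hospitalisations, NYHA stage, treatment and adherence, and ends with "weight and obesity between the groups with longitudinal random-effects models described previously". Deaths have their own method clause within that sentence. It mentions neither a frailty nor a robust variance.

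On age, the Discussion cites a primary-care heart-failure study with a mean of 78.5 years and adds that "our study population will probably have a comparable age".

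**The concern.** A patient who dies of a cause other than heart failure can no longer die of heart failure. Kaplan-Meier treats that patient as censored, and so as someone whose later risk resembles that of patients still alive. The complement of the curve then estimates the risk in a setting where nobody dies of anything else. It is never below the actual probability of heart-failure death, and it lies strictly above it once a heart-failure death follows a competing one. In a population expected to be near 78 years old, non-heart-failure deaths are foreseeable.

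At stake is the absolute risk of heart-failure death in each arm, should it be read off the curve. The excess grows with the number of competing deaths, so it can differ between arms. The Discussion says interpretation will rest on the size of effects as well as on significance, so absolute risks may well be read.

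The secondary concern is the standard error. If deaths within a practice are correlated, a Cox model that treats patients as independent gives intervals that are too narrow and a test that rejects too often.

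**Working it through.** The article states no death rate, event count or power for mortality, so there is no figure of the plan's own to reproduce. The inputs marked as assumed below are not in the document.

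**1. Kaplan-Meier against cumulative incidence for heart-failure death**

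Inputs: follow-up of 19 months (article); total 19-month mortality T of 5-30% (assumed); share s of deaths due to heart failure of 30-70% (assumed); cause-specific hazards in a constant ratio over time (assumed).

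- Cumulative incidence = s × T
- 1-KM = 1 − (1 − T)^s

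| T | s | 1-KM | Cumulative incidence | Excess (points) | Relative |
|---|---|---|---|---|---|
| 5% | 30% | 1.53% | 1.50% | 0.03 | 1.8% |
| 5% | 70% | 3.53% | 3.50% | 0.03 | 0.8% |
| 10% | 50% | 5.13% | 5.00% | 0.13 | 2.6% |
| 20% | 50% | 10.56% | 10.00% | 0.56 | 5.6% |
| 25% | 40% | 10.87% | 10.00% | 0.87 | 8.7% |
| 30% | 30% | 10.15% | 9.00% | 1.15 | 12.8% |
| 30% | 50% | 16.33% | 15.00% | 1.33 | 8.9% |
| 30% | 70% | 22.09% | 21.00% | 1.09 | 5.2% |

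Over the whole range the excess is 0.03 to 1.33 points. With 200 patients per arm, the largest value amounts to 200 × 0.0133 = 2.7 patients.

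**2. How this compares with sampling error**

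For a 10% risk in 200 patients, ignoring clustering, the standard error is √(0.10 × 0.90 / 200) = 2.1 points, against an excess of 0.87 points at T = 25%, s = 40%.

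For the contrast between arms, take T = 25% in one arm and 20% in the other, with s = 40% in both. The excesses are 0.87 points and 1 − 0.80^0.4 − 0.08 = 0.54 points. The risk difference shifts by 0.87 − 0.54 = 0.33 points. Its standard error is √(0.10 × 0.90 / 200 + 0.08 × 0.92 / 200) = 2.9 points.

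**3. Cox test without a practice term**

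Inputs: five patients per practice (article); ICC for death of 0.01-0.05 (assumed; the article's 0.10-0.20 is for quality of life).

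- Design effect = 1 + (5 − 1) × ICC
- Type I error = 2Φ(−1.96 / √design effect)

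| ICC | Design effect | Type I error of a nominal 5% test |
|---|---|---|
| 0.01 | 1.04 | 5.5% |
| 0.02 | 1.08 | 5.9% |
| 0.05 | 1.20 | 7.4% |

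With four patients left per practice after 20% dropout, the ends of this range become 5.3% and 6.8%.

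As a check on direction, the Cox score test was simulated with 80 practices of five, death risk of 10% or 20%, a gamma frailty by practice and 4,000 runs per scenario. With assumed frailty variances of 0.25 to 1.0, the naive test rejected in 5.9% to 12.1% of runs under no effect. With a cluster-robust variance it rejected in 4.6% to 5.0%.

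**The case against.** **On Kaplan-Meier.** The comparison between groups comes from the Cox model, and its cause-specific hazard ratio is valid when other deaths are censored. Kaplan-Meier is the right estimator for all-cause death. What remains is one curve for one secondary outcome, and the article does not say that 1-KM will be reported as a 19-month risk. The trial excludes NYHA stage IV and institutionalised patients, so mortality may sit at the low end of the assumed range, where the excess is negligible. All of this stands, and it limits the point to the absolute-risk display. It does not remove the point, because the estimator is named for heart-failure death rather than left open.

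**On clustering.** A condensed article may leave a frailty or robust variance to the full plan, and the article refers to a statistical analysis plan. It plainly recognises clustering in the randomisation, the sample size and the main models. This also stands, and it makes the second point the weaker one. Still, the sentence attaches random effects to the other secondary outcomes and gives deaths a separate method without any. The models it refers back to are linear models for repeated scores, which cannot be the Cox model.

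**Stronger readings that the article does not support.**

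- A reader might infer that the hazard ratio for heart-failure death is biased. It is not, as a cause-specific hazard ratio.
- A reader might infer that deaths will be analysed as independent. The article only fails to name a practice term.
- A reader might apply the quality-of-life ICC of 0.10-0.20 to deaths and obtain a type I error of 9.8-14.4%. Nothing in the article transfers that ICC to mortality.

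**Conclusion.** The point holds as a minor one. Kaplan-Meier, as named, is the wrong estimator for the absolute risk of heart-failure death. The direction of the error is certain once competing deaths precede heart-failure deaths. The size, 0.03 to 1.3 percentage points, rests on assumed total mortality of 5-30%, a heart-failure share of 30-70% and proportional cause-specific hazards. It is below the sampling error of the arm-specific risk in the example worked, and it would matter only if the curve is read as a risk. No conclusion about the primary outcome, all-cause death or the cause-specific hazard ratio depends on it.

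The missing practice term is a secondary point of wording. Type I error of 5.5-7.4% follows only if deaths do cluster by practice, with an ICC of 0.01-0.05 that the article does not give.

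**What to change.** In Statistical analysis, separate the two death outcomes:

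- All-cause death: keep Kaplan-Meier and the Cox model.
- Heart-failure death: show the Aalen-Johansen cumulative incidence by arm, with non-heart-failure death as the competing event. Keep the Cox model and label its result a cause-specific hazard ratio.
- Both Cox models: state a practice-level robust variance or a shared practice frailty.

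If the full analysis plan already has the practice term, a cross-reference is enough for the last item. The cost is a few lines of analysis wording and code. Date and cause of death are already needed for the outcomes as defined, so no new data are required, and design and sample size do not change.
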